#### Outcome assessments/measurement

All of the outcomes will be assessed twice before and after the intervention treatment.

### Primary outcome

#### Pittsburgh Sleep Quality Index

The Pittsburgh Sleep Quality Index (PSQI), a self-rated questionnaire that evaluates sleep quality and disturbance over 1 month [20], is applied as the primary outcome measurement for clinical effectiveness assessment. The constructive validity and reliability of the PSQI to measure changes of sleep quality have been confirmed in previous studies all over the world. It is widely used to measure response to treatment in research studies and clinical trials. The PSQI is comprised of 19 items which consist of the following seven component scores: subjective sleep quality, sleep latency, sleep duration, sleep efficiency, sleep disturbance, use of hypnotic medication, and daytime dysfunction. Each item is weighted equally on a 4-point scale, from 0 to 3, with 0 indicating no dysfunction and 3 indicating the worst dysfunction. The seven component scores are then added to provide a global PSQI score. In general, a lower global score reflects a better sleep quality [21].

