## Background

Every woman has to undergo the menopausal transition as an inevitable stage of life. During this period, perimenopausal females usually complain of difficulties initiating and/or maintaining sleep with frequent nocturnal and early morning awakenings. Sleep disturbances are often multifactorial in origin and have a significant impact on the health-related life quality. The Study of Women’s Health across the Nation (SWAN) presents that the prevalence of sleep disturbance ascends with increasing age. Recent reviews revealed that the prevalence of insomnia in the perimenopausal women ranges from 39 to 47% [1], while it is approximately 35% in the general population [2].

In addition, with the increasing socioeconomic stress, there are more and more middle-aged women suffering from mood disorders, such as anxiety and depression, which have been noted to be closely related to sleep problems in postmenopausal women [3]. Difficulty in falling sleep has been shown to associate strongly with anxiety, with nonrestorative sleep also correlating strongly with depression, as well as results in anxiety, irritability, and nonrefresh sleep problems which in turn may manifest as depression [4]. Studies by Guidozzi et al. [5] also showed a significant correlation between depression and sleep-related disorders. According to these findings, sleep difficulties and emotional problems interact with and aggravate each other.

Currently, hypnotic medication such as benzodiazepine receptor agonists (estazolam in particular) has been recommended to be the first-choice medicine used routinely for chronic insomnia. Although estazolam is efficacious in the short-term management of insomnia, there is very limited evidence for long-term treatment efficacy [6]. Additionally, various adverse effects related to their use have been reported, including residual daytime sedation, cognitive impairment, and medication dependence [7–10]. Therefore, a large number of patients with insomnia are turning to complementary and alternative medicine such as acupuncture rather than hypnotic medication.

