#### Control group

The participants in the control group will be prescribed oral administration of estazolam tablets (1 mg 30 minutes before sleep once per day for 4 weeks; 2 mg for severe insomnia) which are commonly used for insomnia. The estazolam tablets are produced by Forth Medicine Pharmacy CO.., Ltd (Changzhou, China) (Approval No.: H32020450).

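### The primary PSQI total counts hypnotic use as sleep dysfunction while only the control arm is assigned a nightly hypnotic, so the primary contrast is biased towards acupuncture by up to 3 of 21 points

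*Protocol article*

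**What the plan says.** The protocol article, under Pittsburgh Sleep Quality Index, makes the PSQI the primary measure of clinical effectiveness and describes it as "a self-rated questionnaire that evaluates sleep quality and disturbance over 1 month". The last four of its seven components are "sleep efficiency, sleep disturbance, use of hypnotic medication, and daytime dysfunction". On scoring it says: "Each item is weighted equally on a 4-point scale, from 0 to 3, with 0 indicating no dysfunction and 3 indicating the worst dysfunction". It then says: "The seven component scores are then added to provide a global PSQI score". The direction is that "a lower global score reflects a better sleep quality".

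Under Control group, estazolam is prescribed as "1 mg 30 minutes before sleep once per day for 4 weeks; 2 mg for severe insomnia". The Background names estazolam as a leading example of hypnotic medication. The Intervention group section assigns no drug. The section on outcome assessments places the measurements before and after treatment, so the post-treatment recall month is essentially the dosing period.

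Statistical analysis plans a two-sided comparison of the arms at 0.05. Neither that section nor the PSQI section removes the medication component, analyses it separately or gives a total without it.

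**The concern.** One component of the primary score measures something that the protocol itself assigns to one arm. A control participant who takes the tablets as prescribed reports hypnotic use and is scored as sleeping worse for it. A participant in the acupuncture arm has no assigned hypnotic to report. The between-arm difference in PSQI is then a mixture of two things: the difference in sleep, and an offset created by the scoring rule.

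This is bias, not noise. A larger sample would not reduce it. The planned ANCOVA adjustment for baseline would not remove it either, because the difference arises after randomization. A significant result for acupuncture could not be read as better sleep, and a null result could hide a real advantage of estazolam. There is also a knock-on effect: under fMRI data processing, clinical outcomes that differ significantly are carried into regressions on the brain measures, so the offset could reach the mechanistic aim as well.

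**Working it through.** The protocol gives no effect size, SD or power for the PSQI. Its 40 participants rest on a minimum from earlier fMRI studies plus an allowance for withdrawal. There is therefore no plan figure to reproduce, and the check is of the size of the offset and its effect on the test.

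**Inputs from the protocol article**
- Seven components, added. The 0–3 scale is stated for items; I read it as applying to each component.
- 20 participants per arm (Sample size).
- Two-sided test at 0.05 (Statistical analysis).

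**Inputs that are assumptions**
- Offset from the medication component: 1, 2 or 3 points. The protocol does not say what frequency of use earns each score.
- SD of the PSQI total: 2.5 to 5 points, the same in both arms.
- No difference between arms in the other six components.
- A baseline medication component near 0 in both arms. This is inferred from the exclusion of psychoactive medication in the previous 3 months.

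**Step 1: largest possible offset.** The maximum total is 7 × 3 = 21. One component contributes at most 3, and 3/21 = 14% of the range.

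**Step 2: the test.** With two arms, one-way ANOVA is equivalent to the two-sample t test with 20 + 20 − 2 = 38 degrees of freedom. The standard error of the difference is SD × √(2/20), and the noncentrality parameter is offset / [SD × √(2/20)]. The chance of a significant result favouring acupuncture is the probability that a noncentral t variable with 38 degrees of freedom exceeds the 97.5% point of the central t.

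**Step 3: results, 20 per arm.**

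| Offset | SD 2.5 | SD 3 | SD 4 | SD 5 |
|---|---|---|---|---|
| 3 points | 95.9% | 86.9% | 63.7% | 45.6% |
| 2 points | 69.3% | 53.8% | 33.8% | 23.4% |
| 1 point | 23.4% | 17.6% | 11.7% | 9.0% |

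The nominal rate in this one direction is 0.05/2 = 2.5%. Every cell exceeds it.

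**Step 4: smallest significant observed difference.** At 20 per arm it is 1.92, 2.56 and 3.20 points for SD 3, 4 and 5. A 3-point offset alone exceeds it for an SD up to 4, but not for an SD of 5.

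**Step 5: allowing for withdrawal.** If 16 per arm complete (20% loss, an assumption), the figures for SD 3 to 5 are 78.1% to 37.6% for 3 points, 44.6% to 19.4% for 2 points and 14.8% to 7.9% for 1 point. The conclusion is unchanged.

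**Step 6: masking.** If estazolam were truly better by d points on the six other components and the offset is o, the expected seven-component advantage of estazolam is d − o. With d = 3 and o = 3 it is zero.

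**Step 7: without the component.** The score then runs from 0 to 6 × 3 = 18. Under the same null, the chance of a significant result favouring acupuncture returns to 2.5%.

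**The case against.** The strongest reply concerns size. The protocol does not give the anchors of the medication item, so it is tempting but unsupported to say that an adherent control participant must score 3. From the document alone the offset lies somewhere between 0 and 3 points. No SD is given either, so no single false-positive rate can be quoted. Both points stand, and they are why a range is shown.

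A second reply is that the baseline may not be near zero. A reader might infer that current hypnotic users are excluded outright. The relevant exclusion criterion joins recent acupuncture and current hypnotic treatment with an 'and', so it does not clearly say that. The inference rests on the separate 3-month psychoactive-medication criterion, which does not name hypnotics. This stands as a limit on the size, but the assigned difference between arms after randomization remains.

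A third reply is that an analysis plan not shown here might handle the component, and that the Hypothesis section ties the difference between treatments to fMRI. However, the PSQI section positively describes a sum of all seven components, and Statistical analysis plans between-group tests. The point rests on what is written, not on an omission. The mattress monitoring is free of this component, but it is secondary and does not correct the primary comparison.

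A reader might also infer that the component reveals allocation to the blinded assessor or statistician. Nothing supports this: the PSQI is self-rated, and no section says that either of them sees item-level answers.

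**Conclusion.** The concern holds. The scoring rule and the choice of comparator together bias the primary contrast towards acupuncture, by an amount that is at most 3 of 21 points and cannot be fixed more closely from the document. Under the stated assumptions the chance of a false result for acupuncture is about 96% to 46%, 69% to 23% or 23% to 9% for offsets of 3, 2 or 1 points, against 2.5%. The direction follows from the protocol's own text; the size depends on the assumed item score, SD and near-zero baseline.

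It would go too far to say that the trial will show acupuncture superior. It can do so without any difference in sleep, and it can equally conceal a benefit of estazolam. The problem should be corrected before data lock, because otherwise the primary result cannot be interpreted as an effect on sleep.

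**What to change.** Before data lock, and without reference to outcome data by arm, define the primary endpoint as the sum of the six PSQI components other than hypnotic use (range 0–18), scored in the same way in both arms and at every visit where the PSQI is taken. Report the seven-component global score and the medication component separately as secondary results, and state that the global score includes the assigned treatment in one arm.

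The cost is moderate. All components are collected already, so no new data, visits or changes to treatment are needed. However, the trial is registered and recruiting, with participants and clinicians unblinded, so this must be a dated and documented endpoint amendment with its reason given. The six-component sum is also less directly comparable with published PSQI totals, and the protocol's statement about the validity of the PSQI does not extend to it. Reporting the global score alongside limits the loss of comparability.

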### Secondary outcome

#### Micro-movement sensitive mattress-type sleep monitoring system

All of the study subjects will be measured for two nights (baseline: after randomization and before treatment, after the completion of treatment) in a sleep laboratory with a sound-attenuated, light-controlled, and temperature-controlled room. The TDM-6000 micro-movement sensitive mattress-type sleep monitoring system (MSMSMS) will be conducted to precisely obtain the continuous dynamic physiological parameters of the patients at night, as well as to compare the proportion of deep sleep, light sleep, and rapid eye movement (REM) sleep during the sleep period. During assessment, patients will be permitted to sleep optionally based on their habitual sleep time, with the recording time ranging from the moment of patient lying on the bed to the time of getting up. Sequentially, we can analyze the sleep architecture/structure, and accurately identify the various kinds of sleep disorders.

#### Hamilton Depression Scale and Hamilton Anxiety Scale

Changes in levels of mood disorder will be measured on the Hamilton Depression Scale (HAMD) and the Hamilton Anxiety Scale (HAMA).

There are three types of HAMD scale, each with 17, 21, or 24 items. The 24-item HAMD scale will be used to evaluate the depressive condition in this trial. According to the score standard, a normal score is <8; a score ≥8 and <20 indicates that the patient has mild depression; a score ≥20 and ≤35 indicates that the patient has moderate depression; and a score >35 indicates that the patient has severe depression. Typically, the higher score reflects the more severe depression [22].

To assess anxiety, there is a 14-item self-rating questionnaire for evaluating the anxiety condition of last week. Based on the score standard, answers are scored on a 0–4 scale, with 0 indicating no symptoms and 4 indicating the worst anxiety condition, with a range in total score from 0 to 56.

In general, the normal threshold is 6 points; scores ranging from 0 to 5, from 6 to 13, from 14 to 20, from 21 to 28, and as 29+ are typically used to rate anxiety as none, mild, moderate, severe, and extremely severe, respectively. In general, the higher the score, the more severe the anxiety is.

In this study, both HAMD and HAMA will be evaluated twice (before and after treatment).

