**Methods/Design:**

This study is a randomized, assessor–statistician-blinded, positive medicine controlled trial involving 40 participants. A total of 40 eligible patients with perimenopausal insomnia will be randomly assigned to two groups in a 1:1 ratio as an intervention group using acupuncture and a control group taking estazolam. Participants in the intervention group will receive six acupuncture treatment sessions per week for 4 consecutive weeks, for a total of 24 sessions during the study. Meanwhile, the medicine control group will be prescribed estazolam 1–2 mg/day to be taken 30 minutes before sleep for 4 weeks. The primary outcome is the Pittsburgh Sleep Quality Index. Secondary outcomes are the micro-movement sensitive mattress-type sleep monitoring system, the Hamilton Depression Scale, and the Hamilton Anxiety Scale. All outcomes will be evaluated before and after treatment. The safety of interventions will be assessed at every visit.

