### Setting

A total of 40 patients diagnosed with perimenopausal insomnia will be divided randomly into two groups (acupuncture intervention group and western medicine control group) through a completely randomized digital table in a ratio of 1:1. This RCT will be conducted in a single center with the assessor and statistician blinded to treatment allocation, and will be carried out in Sichuan Integrative Medicine Hospital, Chengdu, Sichuan, China.

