#### Inclusion criteria

Patients meeting all of the following criteria will be enrolled in the study:Patients meeting the diagnostic criteria for primary insomnia in the *Diagnostic and Statistical Manual of Mental Disorders*, fifth edition [15].Patients meeting the diagnostic criteria for perimenopausal syndrome according to the 2011 criteria of the International Menopause Society [16] and the 2001 criteria of the North American Menopausal Society [17].Chief complaint of sleep disorder.Dextromanuality.Female aged between 40 and 55.The Hamilton rating scale for depression (HAMD) score should be 8 points or higher.The Hamilton rating scale for anxiety (HAMA) count should be 6 points or higher.Voluntarily participating in this study with a written informed consent form signed by the participants themselves.

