### Blinding

Considering the significant difference of treatment and the specificity of acupuncture, double blinding of the clinician and patient is unfeasible. However, to guarantee the integrity of this trial, we will strictly conduct randomization allocation and appoint different people to perform therapy, assessment, and statistical analysis according to the principle of blinding.

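### As written, the anxiety scale (HAMA) is scored by patients who know their treatment, so the trial's assessor blinding does not cover it, nor the self-rated PSQI

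*Protocol article*

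**What the plan says.** The article names the HAMA as a secondary outcome; the abstract lists "the Hamilton Depression Scale, and the Hamilton Anxiety Scale. All outcomes will be evaluated before and after treatment". The section on the two Hamilton scales then describes how anxiety is measured: "To assess anxiety, there is a 14-item self-rating questionnaire for evaluating the anxiety condition of last week", with items scored 0 to 4, "with a range in total score from 0 to 56", and a normal threshold of 6 points. It does not say who completes the HAMD.

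On blinding, the Setting section describes a single-center trial "with the assessor and statistician blinded to treatment allocation". The title line of the abstract's methods and the opening of the Discussion use the same label, and none of these places excepts an outcome. The Blinding section concedes that "double blinding of the clinician and patient is unfeasible" and provides for different people to deliver treatment, assess outcomes and analyze data.

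The Primary outcome section states that the PSQI is self-rated. The limitations paragraph of the Discussion acknowledges a high risk of bias because participants are not blinded. Its answers are strict randomization, separation of roles, and closer contact with the control group.

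**The concern.** For a self-rated scale the patient is the assessor. If patients know their treatment and score their own anxiety, the statement that the assessor is blinded is untrue for that outcome, whoever handles the form afterwards.

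This matters more here than in many trials because the primary outcome is already self-rated and unblinded. The secondary scales are where a blinded scorer could add something. The mood scales also carry the trial's claim about emotional circuits, and the fMRI data processing section relates brain changes to those clinical outcomes that differ significantly. A HAMA difference produced by expectation could enter that analysis.

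The arms differ visibly: 24 needling sessions in one, tablets with weekly visits and daily contact in the other. The Discussion itself says that the closer relationship in the acupuncture arm is likely to improve the therapeutic effect. A reader who relies on the assessor-blinded label would give the anxiety result more credit than its method of scoring allows.

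**Working it through.** The point rests on setting sections side by side; the article gives no figure to reproduce.

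**1. Is the self-rated questionnaire the trial's HAMA?** The sentence does not repeat the scale's name, so this has to be established.
- It stands under the Hamilton heading, and no other anxiety instrument is named anywhere.
- Its items and range agree: 14 items × maximum 4 = 56, matching the stated upper limit.
- Its threshold of 6 points matches the HAMA entry rule in the Inclusion criteria ("count should be 6 points or higher").

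The sentence therefore describes the HAMA used here.

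**2. Who scores it, and does that person know the allocation?** By the section's own description, the patient scores it. By the Blinding section, the patient is not blinded.

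**3. Does the blinding claim allow for this?** The Setting section reads "This RCT will be conducted in a single center with the assessor and statistician blinded to treatment allocation". Neither it, the abstract nor the Discussion names an exception. Steps 1 to 3 cannot all stand as written.

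**4. Does the stated remedy repair it?** Keeping acupuncturist, assessor and statistician apart protects outcomes that the assessor scores. It has no effect on a form scored by the patient.

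**5. Illustration of size.** Inputs: 20 per arm (Sample size section) and a two-sided 5% level (Statistical analysis section). The net between-arm shift in reported score, in SD units, is an assumption; the documents give none. With no true treatment difference, a two-sample t test has 20 + 20 − 2 = 38 degrees of freedom and critical value 2.024. The noncentrality parameter is shift × √(20/2) = shift × 3.162.

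| Assumed net shift (SD) | Noncentrality | Probability of a significant result |
|---|---|---|
| 0 | 0 | 5% |
| 0.2 | 0.632 | 9.5% |
| 0.3 | 0.949 | 15.2% |
| 0.5 | 1.581 | 33.8% |

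The table shows what a net expectation effect of that size would do to any outcome exposed to it. It does not compare self-rating with interview.

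**The case against.** **A wording slip.** The sentence reads as a general description of an instrument, not as a procedure. The same section says that both Hamilton scales will be evaluated before and after treatment, the Procedure section speaks of patients being evaluated by scales, and separate people are appointed to assess. One wrong adjective could explain everything. That is possible, and it cannot be settled from the article. But the self-rating statement is explicit, and nowhere does the article say that the assessor scores the HAMA. If it is a slip, the section still has to be corrected.

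**Already disclosed.** The Discussion admits the risk from unblinded participants. This stands and softens the point. The disclosure is general, however: it does not say that any outcome falls outside assessor blinding, and it offers a remedy that does not work for a self-rated scale.

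**An interview does not remove the bias.** A blinded interviewer still scores what an unblinded patient reports. This stands in full. A reader might take 9.5% to 34% as the penalty for self-rating, or as the gain from changing the rater. The documents support neither. The range is the whole of an assumed net expectation effect, much of it could apply to an interviewed scale too, and both arms receive a known active treatment, so even its direction is not given.

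**Eligibility.** A reader might infer that a self-scored HAMA also compromises entry to the trial. It does not create allocation bias: eligibility is verified before the randomization envelope is opened, so no allocation is known when the entry score is taken.

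**HAMD and mattress recording.** A reader might also assume that these are blinded. The article names the scorer of neither, so it does not support that assumption.

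**Conclusion.** The point holds in a limited form. Taken as written, the article has the HAMA scored by unblinded patients while claiming assessor blinding without exception, so the claim does not cover the HAMA or the PSQI. This is a positive contradiction within the article, not detail left to a fuller document.

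It concerns one secondary outcome directly, and the reach of the blinding label generally. The size of the bias is unknown: the false-positive range above depends wholly on an assumed shift of 0.2 to 0.5 SD. What can be recovered is the removal of scorer bias and an accurate label, not freedom from expectation effects. The conclusion assumes that the self-rating sentence means what it says; if it does not, the correction is one of wording. The change is worth making because the separate assessor is already provided for.

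**What to change.** 1. In the section on the Hamilton scales, state that the separate blinded assessor scores the HAMA and HAMD by interview before and after treatment, and that patients are asked not to reveal their treatment.
2. Use the same mode at both time points for any one patient. Recruitment has begun (Trial status), and a self-rated baseline followed by an interviewed outcome would mix modes within the before-after comparison. If the HAMA must stay self-rated for patients already enrolled, declare it for them an unblinded patient-reported outcome.
3. In the abstract and the Setting section, limit the assessor-blinded description to outcomes actually scored by a blinded assessor, and say that the PSQI is not among them. Include the mattress recording only if its scorer is in fact blinded. Bring the Discussion into line.

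The cost is wording, a few minutes of the existing assessor's time per visit, and care over consistent mode. No extra staff are needed.
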